#### Secondary Outcomes

The secondary outcome is the effectiveness of the PLR, which will be determined by comparing changes in outcomes reported from week 4 to week 10 by patient participants in the experimental arm to those reported by participants in the control arm. Details of these outcomes are listed in Textbox 3.

Secondary outcomes of the effectiveness of the phallus length reducer.
**Outcomes and explanations**
Deep dyspareunia: an 11-point numeric rating scale, wherein 0 corresponds to no pain and 10 corresponds to the worst pain, will be used to measure deep dyspareunia intensity (using an item previously published by our team [18]); mean dyspareunia scores from weeks 1 to 4 will be compared with those from weeks 5 to 10 in the control and experimental armsSexual function: total score on the Female Sexual Function Index, a 19-item self-report measure that captures information on sexual desire, arousal, lubrication, orgasm, satisfaction, and pain over the past 4 weeks [22]Sexual distress: total score on the Female Sexual Distress Scale-Revised, a 13-item self-report measure that captures sex-related personal distress over the past 4 weeks [23]Anxiety: total score on the Generalized Anxiety Disorder-7, a 7-item questionnaire validated for monitoring the severity of general anxiety [24]Depression: total score on the Patient Health Questionnaire-9, a 9-item questionnaire validated for monitoring the severity of depression [25]

#### Substudy Outcomes

The substudy will explore the acceptability and the preliminary convergent validity and test-retest reliability of a vaginal insert for the self-assessment of deep dyspareunia. The vaginal insert acceptability substudy outcome is based on an 18-item, built-for-purpose questionnaire adapted from a previously published measure for assessing the acceptability of female condoms [21] on a response scale ranging from 1 to 5. This questionnaire will be completed by all patient participants by week 4 (Multimedia Appendix 1).

Participants will use the vaginal insert to palpate various pelvic organs and structures (ie, to palpate the bladder anteriorly, the pelvic floor laterally, the pouch of Douglas posteriorly, and the cervix at the apex of the vagina) that have been previously associated with deep dyspareunia [26], and they will indicate whether they feel pain (“yes” or “no”) and the severity of the pain (11-point numeric rating scale wherein 0 corresponds to no pain and 10 corresponds to the worst pain). The number of tender sites for each participant will be calculated based on the self-reported number of tender anatomic sites that the participants identify when using the insert. Data on clinically assessed tenderness (“yes” or “no”) for each participant were previously collected through digital pain mapping, which was completed by a clinician. Data for clinically assessed tenderness are stored in EPPIC. These pain-related variables will be used to assess the convergent validity and test-retest reliability of the vaginal insert.

### Assignment of Interventions

The study coordinator will use a REDCap (Research Electronic Data Capture; Vanderbilt University) extension package called *randomization* to randomly assign consented participants in a 1:1 ratio to 1 of 2 study arms; the experimental PLR arm will receive the PLR, and the waitlist control arm will receive the PLR once the study has concluded. Both arms will receive the vaginal insert for the substudy.

### Participant Timeline

Throughout the study, all participants will continue concurrent endometriosis treatments and treatments for other conditions as usual. At the start of the study, both arms will complete baseline demographic, psychological, and sexual function questionnaires. In weeks 1 to 4 of the study, patient participants in both arms will engage in sexual activity as usual and be asked to record a daily diary of all sexual events and the severity of deep dyspareunia (score: range 0-10). Psychological and sexual function questionnaires will be repeated at the end of week 4. In week 5, participants in the experimental arm will receive and begin to use the PLR. Participants in the waitlist control arm will not receive the PLR and will continue to record deep dyspareunia severity at each sexual encounter. At the end of week 10, all patient participants will repeat the psychological and sexual function questionnaires, and participants in the experimental arm will indicate the acceptability of the PLR. At the conclusion of the study period, participants in the waitlist control arm will receive the PLR.

For the substudy, during weeks 1 to 4, all patient participants will self-assess deep dyspareunia by using the vaginal insert on weeks 2 and 3 of their menstrual cycle or on another two occasions (1 week apart) in the absence of regular bleeding. At the end of week 4, all patient participants will indicate the acceptability of the vaginal insert. The participant timeline is depicted in Table 1.

**Table 1 table1:** Schedule of interventions and assessments.

Groups and activities					Weeks 1 to 4							Weeks 5 to 10		
					Start of study		Vaginal insert self-assessment		Midstudy questionnaire		Experimental period			End of study
**Group 1 (PLR^a^ group)**														
	**Patients**													
		Informed consent		✓										
		Demographics form		✓										
		Study diary		✓		✓		✓		✓			✓	
		Vaginal insert self-assessment (twice)				✓								
		Receive and use PLR								✓				
		**Questionnaires**												
			FSFI^b^	✓				✓					✓	
			FSDS^c^	✓				✓					✓	
			PHQ-9^d^	✓				✓					✓	
			GAD-7^e^	✓				✓					✓	
			Vaginal insert feedback form					✓						
			PLR feedback form										✓	
	**Partners**													
		Informed consent		✓										
		Demographics form		✓										
		PLR feedback form											✓	
**Group 2 (control group)**														
	**Patients**													
		Informed consent		✓										
		Demographics form		✓										
		Study diary		✓		✓		✓		✓			✓	
		Vaginal insert self-assessment (twice)				✓								
		Continue sex as usual								✓				
		Receive PLR											✓	
		**Questionnaires**												
			FSFI	✓				✓					✓	
			FSDS	✓				✓					✓	
			PHQ-9	✓				✓					✓	
			GAD-7	✓				✓					✓	
			Vaginal insert feedback form					✓						
	**Partners**													
		Informed consent		✓										
		Demographics form		✓										

^a^PLR: phallus length reducer.

^b^FSFI: Female Sexual Function Index.

^c^FSDS: Female Sexual Distress Scale.

^d^PHQ-9: Patient Health Questionnaire-9.

^e^GAD-7: Generalized Anxiety Disorder-7.

### Confidentiality

The list of potential participants is password protected and stored on a secure server at the study site, and it will only be available to select members of the research team. Upon enrollment to the study, each participant will be given a unique study ID number that does not correlate to any personally identifying information. All reports, data collection sheets, and administrative forms will be identified by this number to maintain confidentiality. This ID number can only be decrypted by a password-protected linking file, which is stored separately on the secure server at the study site; similarly, it will only be available to select members of the research team.

### Data Management

Study materials, such as the instruction booklet, the daily diaries, and the PLR, will be mailed to the participants, depending on their study arm allocation. The study coordinator will follow up with each participant to collect the daily diaries of the control and intervention group participants upon the completion of the study. We will not blind the research team to the study arm allocations. Once the participants have completed the study, a research team member will extract the data from the daily diaries and upload the data onto a Microsoft Excel (Microsoft Corporation) sheet. The data will be stored on a secure server at the study site, and they will only be available to select members of the research team. Details of the data management procedures can be found in the study’s research ethics board application, which can be provided upon request. We do not anticipate any adverse events with the use of the PLR, and as such, we will not need a data monitoring committee. If any adverse events occur, the participants can record them in the daily diary, and they will have the contact information of the study team to debrief such cases.

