### Effectiveness of Using a PLR to Reduce Deep Dyspareunia

For the experimental and waitlist control arms, the difference in deep dyspareunia scores from week 4 to week 10 between the two arms will be assessed by using an analysis of covariance (ANCOVA)–based approach [27]. We will compare mean scores from weeks 5 to 10 between the two arms, using preintervention (weeks 1-4) mean scores as covariates in the model. Similar ANCOVA modeling will be used for the Female Sexual Distress Scale-Revised, Female Sexual Function Index, Generalized Anxiety Disorder-7, and Patient Health Questionnaire-9 scores. If the assumptions of the ANCOVA model are not met by the data set, then we will consider conducting other appropriate statistical analyses, such as the ANOVA-based approach, 2-tailed *t* tests, linear regression modeling, and nonparametric approaches for the ANCOVA model.

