The strengths of the protocol include having a randomized design, taking prospective pain measurements at each sexual encounter, and supplementing the trial by embedding the vaginal insert as a potential novel self-assessment tool. One limitation of the protocol is that it is not placebo controlled; however, it would be difficult to design a placebo for the PLR. Another limitation is that we will be comparing the vaginal insert to clinical examinations that are done at entry into the registry, which may be conducted several months before enrollment into the trial. In a future study, a pelvic examination can also be performed at recruitment. Furthermore, a limitation of the pilot trial is that we will not control for variables like age and BMI, which are potential confounders that may affect the use of the vaginal insert or PLR.

In summary, the PLR may be a noninvasive self-management tool for people with endometriosis-associated deep dyspareunia. The results of our pilot RCT will inform a future full-scale RCT of both the PLR and the vaginal insert test. The results from our study will be reported in peer-reviewed journals, in conference presentations, and to the study participants and the public through plain-language knowledge translation strategies. Ultimately, these innovations will contribute to the body of work on the rigorous investigation and evidence-based management of endometriosis-associated deep dyspareunia.

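### Pain diaries are collected and extracted only at completion, so the weeks 1–4 baseline covariate stays open during unblinded device use and withdrawn couples' scores may not be retrieved

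*Protocol article*

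**What the plan says.** All references are to the protocol article.

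- **Handling of the diary (Data Management).** "Study materials, such as the instruction booklet, the daily diaries, and the PLR, will be mailed to the participants", according to allocated arm. The coordinator is to follow up with each participant to "collect the daily diaries of the control and intervention group participants upon the completion of the study". Then: "Once the participants have completed the study, a research team member will extract the data from the daily diaries", for entry in a spreadsheet. The same paragraph states: "We will not blind the research team to the study arm allocations". It refers the reader to the ethics board application for further data management details.
- **Content and timing (Participant Timeline, Table 1).** In weeks 1–4 patients in both arms will "be asked to record a daily diary of all sexual events and the severity of deep dyspareunia". Table 1 ticks the study diary in every period from start to end of study. "In week 5, participants in the experimental arm will receive and begin to use the PLR". Questionnaires are due at the end of week 4, but no return, copy or closing of the diary is mentioned there.
- **Use in the analysis (Effectiveness of Using a PLR to Reduce Deep Dyspareunia).** Mean scores from weeks 5–10 are compared between arms, "using preintervention (weeks 1-4) mean scores as covariates in the model".
- **Claimed strength (Discussion).** The strengths listed include "taking prospective pain measurements at each sexual encounter".

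**The concern.** A baseline covariate should be fixed before treatment can influence it. Here the patient holds her weeks 1–4 record until the end of the trial. In the experimental arm those last weeks are spent using a device she knows she is using. An entry missed in week 3 can be filled in during week 10, or an early score changed in the light of later experience. If such changes differ between arms, ANCOVA passes part of the difference into the estimated treatment effect. The Introduction criticises questionnaires for recall bias, so it matters that the article describes no step that secures the early diary entries.

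The second issue is withdrawal. Sample Size allows for dropout and the Discussion expects that the intensive procedures may reduce retention. Yet the stated triggers for collecting and extracting the diary are both completion. A couple leaving in week 8 could hold a full baseline and several outcome scores that the stated procedure does not clearly bring in. The missing-data rule (pairwise exclusion below 5% missing, multiple imputation above) could then be applied to scores that were in fact written down.

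The pain comparison is not the only use of the diary. Adherence, one of the primary outcomes, is a ratio of counts of sexual events, which the diary records. The vaginal insert substudy correlates tenderness with deep dyspareunia scores.

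**Working it through.** **1. Sequence of events**

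| Time | Event | State of the weeks 1–4 record |
|---|---|---|
| Weeks 1–4 | Events and pain scores entered at home | Being written, held by the patient |
| End of week 4 | Questionnaires repeated | No diary step stated |
| Weeks 5–10 | Experimental arm uses the PLR | Still held by the patient |
| Completion | Diary collected, then extracted | First seen by the team |

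The covariate is thus open to completion or change through weeks 5–10.

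**2. What a shifted baseline would do (illustration)**

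The ANCOVA estimate is (difference in weeks 5–10 means) − b × (difference in weeks 1–4 means), where b is the pre/post slope. If the recorded baseline in the PLR arm moves up by s points and nothing else changes, the estimate moves by −b × s. An upward shift favours the PLR; a downward shift does the reverse.

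The article gives no SD, slope or shift, so these are assumptions: SD 2 points, 20 per arm, slope 0.4 to 0.8, no true effect, shift in the PLR arm only, 4,000 simulated trials per cell.

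| Slope b | Shift s | −b × s | Simulated bias | Two-sided type I error |
|---|---|---|---|---|
| 0.4 | 0 | 0 | 0.001 | 4.9% |
| 0.4 | 0.5 | −0.2 | −0.218 | 7.1% |
| 0.4 | 1.0 | −0.4 | −0.389 | 9.9% |
| 0.6 | 0 | 0 | 0.002 | 4.5% |
| 0.6 | 0.5 | −0.3 | −0.303 | 8.8% |
| 0.6 | 1.0 | −0.6 | −0.598 | 20.6% |
| 0.8 | 0 | 0 | 0.005 | 5.4% |
| 0.8 | 0.5 | −0.4 | −0.406 | 17.4% |
| 0.8 | 1.0 | −0.8 | −0.788 | 49.9% |

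This shows the mechanism, not an expected bias.

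**3. What unretrieved diaries would cost**

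The plan's own figures agree: 2 × 20 = 40 couples, and 2 × 40 = 80 participants. No dropout rate is given. Going from the rule of thumb of 12 per group to 20 leaves room for 1 − 12/20 = 40% loss, which serves here as the top of an assumed range.

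With k of 40 patients lost equally from both arms, the standard error is multiplied by √(40/(40 − k)):

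- 10%, k = 4: √(40/36) − 1 = 5.4% (18 per arm left)
- 20%, k = 8: √(40/32) − 1 = 11.8% (16 per arm left)
- 40%, k = 16: √(40/24) − 1 = 29.1% (12 per arm left)

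These figures count each withdrawer as worth as much as a completer. A patient with no event in weeks 5–10 has no outcome score to recover, and a late leaver's mean rests on fewer events. With equal loss per arm they are therefore upper bounds. Uneven loss costs more: all 8 from one arm gives √((1/12 + 1/20)/(2/20)) − 1 = 15.5%, against 11.8%.

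**The case against.** **Withdrawn couples.** A reader might infer that their pain scores are lost or discarded. The article does not say so. The coordinator follows up with each participant, no rule excludes diaries of couples who leave, and the pain analysis is not restricted to completers. This objection stands: the data are at risk, not lost.

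**Details left elsewhere.** Retrieval at withdrawal, interim copies and dating of entries may be covered in the ethics application, and the participant instructions are in an appendix not shown. This stands for those details; in particular, one cannot say that the diary has no dated entries. It does not remove the timing point, because the article itself places collection and extraction at completion.

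**Prospective by instruction.** The Abstract has severity recorded after each episode of intercourse, and the body asks for a daily diary. A diary collected late is not the same as a recall questionnaire, and nothing shows that back-filling is expected. It would be wrong to infer that the prospective claim is false or that the baseline will be revised. What remains is that no stated step protects the claim.

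**Limits of a week 4 lock.** The weeks 5–10 entries, which form the outcome, stay unblinded and open. The article also does not say whether couples know their arm during weeks 1–4, so a locked baseline may not be free of knowledge of allocation. Both points stand; the lock rules out only changes made after device use.

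**Weight and stage.** This is a secondary estimate in a pilot, and 31 of the planned 40 couples had been recruited by September 2021. Both limit what can be gained now. But the pilot exists to test methods for a definitive trial, and an unsecured baseline would carry over into it.

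**Conclusion.** The point holds as an avoidable weakness in the stated procedure. The weeks 1–4 covariate stays with the participant and could be completed or revised during unblinded PLR use, which weakens the claim of prospective measurement. It is an opportunity for bias that the article does not show to occur. Its size cannot be derived, and the simulated figures depend wholly on assumed shifts, SD and slopes.

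On withdrawal, the supportable statement is that recorded scores from couples who leave in weeks 5–10 are at risk of not being retrieved. The cost in precision is at most about 5%, 12% or 29% in the standard error at 10%, 20% or 40% withdrawal. This assumes that no such diary is recovered, that losses are equal between arms, and that every withdrawer would otherwise have contributed fully. The rates are assumptions.

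The finding supports an inexpensive improvement. It does not show that the trial's estimate is invalid.

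**What to change.** 1. Obtain the weeks 1–4 diary together with the week 4 questionnaires, before PLR use begins, as a photo, scan or dated entry in REDCap (already used for randomisation). Lock that record as the source of the covariate.
2. Collect the remaining diary at week 10 or at withdrawal, whichever comes first, and extract it in either case.
3. State that the pain analysis includes the recorded weeks 5–10 events of every randomised patient, including those who withdraw.
4. For couples already past week 4, seek the diaries of those who withdrew and report the collection timing as a limitation.
5. If the ethics application already provides any of these steps, say so in the article's Data Management section.

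**Cost.** One extra step at an existing assessment point, with slightly more effort for participants and coordinator at week 4. No sample size or analysis model changes. The fix protects the baseline covariate but not the unblinded weeks 5–10 entries.

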**Methods:**

Ours is an investigator-initiated, 2-arm RCT. We will recruit 40 patient participants with diagnosed endometriosis between the ages of 19 and 49 years, as well as their sexual partners. The participating couples will be randomized in a 1:1 ratio into the experimental arm or the waitlist control arm. The length of the study period will be 10 weeks, during which time all participants will record deep dyspareunia severity following each episode of sexual intercourse. In weeks 1 to 4, all patient participants will record deep dyspareunia severity at each sexual encounter. In weeks 5 to 10, participants in the experimental arm will use the buffer during vaginal penetration; participants in the waitlist control arm will continue engaging in vaginal penetration as usual. Participants will complete questionnaires for assessing measures of anxiety, depression, and sexual function at baseline, at 4 weeks, and at 10 weeks. In the substudy, patient participants will self-assess dyspareunia by using a vaginal insert on 2 occasions, at least 1 week apart. The primary outcomes—the acceptability and feasibility of the buffer—will be assessed with descriptive statistics, and the secondary outcome—phallus length reducer effectiveness—will be assessed by using an analysis of covariance–based approach. For the vaginal insert, we will assess acceptability, test-retest reliability, and convergent validity via correlation analyses comparing the use of the insert to clinical examination in terms of dyspareunia assessment outcomes.

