### Interventions

The PLR (brand name: Ohnut) is made of a Food and Drug Administration–approved body- and skin-safe polymer blend. The blend is a thermo-set material that does not contain bisphenol A, phthalates, and latex and can be used with either silicone lubrication or water-based lubrication [20]. The PLR is a buffer that is worn externally over the penis or a penetrating object to limit the depth of penetration.

The vaginal insert is made of polyurethane and is stable from −40 to 70 °C. It will be self-inserted by the patient participants to self-assess the tenderness of pelvic structures implicated in deep dyspareunia that are typically assessed by a clinician during a pelvic examination. This is a novel, off-label use of the device.

To support the use of the vaginal insert and PLR, the study team developed patient-centered study booklets, which include instructions for the use of each tool (Multimedia Appendix 1). The instructions were developed with a gynecologist specialized in the assessment of dyspareunia, a pelvic floor physiotherapist with expertise in guiding patients to use vaginal inserts, and a clinical psychologist with experience in coaching patients and their partners to integrate the PLR in penetration. A medical illustrator was engaged to create diagrams for guiding the use of the vaginal insert.

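### As described, adverse-event capture is passive only: an optional entry in a diary read after completion, or contact that the participant starts

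*Protocol article*

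**What the plan says.** The relevant text is in the protocol article under Data Management. On adverse events it states: "If any adverse events occur, the participants can record them in the daily diary". The same sentence gives a second route: "they will have the contact information of the study team to debrief such cases".

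On timing, the study coordinator is to follow up with each participant to "collect the daily diaries of the control and intervention group participants upon the completion of the study". Reading the diaries comes later still: "Once the participants have completed the study, a research team member will extract the data from the daily diaries".

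The article does without a data monitoring committee on this ground: "We do not anticipate any adverse events with the use of the PLR". That sentence names the PLR only. Under Interventions, the use of the vaginal insert is described differently: "This is a novel, off-label use of the device". According to Participant Timeline, patients in both arms use the insert twice during weeks 1 to 4, and only the experimental arm uses the PLR, from week 5.

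Table 1 lists the study diary for patients in both groups and for no partner. Partners in the PLR group complete a PLR feedback form at the end of the study. Partners in the control group have only consent and a demographics form.

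**The concern.** Both stated routes depend on the participant deciding to report. The wording about the diary is permissive, and no scheduled question about adverse events is described. The article itself gives reasons to expect under-reporting: its Introduction describes reluctance to discuss sexual health and patients who persist with penetration despite severe pain, and Study Setting places all procedures at home, so no visit exists at which a problem might be noticed.

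Two things are at stake. First, an insert-related event that is only written down would stay unknown to the team while later participants begin the same procedure. Second, the pilot is meant to inform the decision on a definitive trial. If few or no events are reported under passive capture, the team cannot tell whether harm was absent or simply not mentioned. The expectation of no adverse events does not fill that gap for the insert, because it was stated for the PLR alone.

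**Working it through.** No sample-size or power formula applies. The check is timeline arithmetic plus a comparison of the stated procedures.

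**Inputs**
- Study length, from the Abstract: "The length of the study period will be 10 weeks". This agrees with Table 1: weeks 1 to 4 (4 weeks) + weeks 5 to 10 (6 weeks) = 10 weeks.
- Insert exposure: within weeks 1 to 4, both arms (Participant Timeline).
- PLR exposure: from week 5 to week 10, experimental arm only (Participant Timeline).
- Diary collected and read: after completion (Data Management). I take this as each participant's own completion, at the end of week 10, which is the reading most favourable to the plan.

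**Formula.** For an event recorded in the diary and not otherwise reported, lag = 10 weeks − weeks elapsed at the event. Time to retrieve and transcribe the diary is extra.

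**Results**
- Insert, start of week 1: 10 − 0 = 10 weeks.
- Insert, end of week 4: 10 − 4 = 6 weeks. The insert range is therefore about 6 to 10 weeks.
- PLR, start of week 5: 10 − 4 = 6 weeks.
- PLR, end of week 10: 10 − 10 = 0 weeks. The PLR range is therefore 0 to about 6 weeks.
- Either device, if the participant contacts the team: lag close to zero.

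**Coverage by group, from Table 1 and Data Management**
- Patients, both arms: diary and self-initiated contact. They also complete questionnaires at weeks 4 and 10, but none is described as asking about adverse events.
- Partners, PLR arm: no diary; self-initiated contact, and a PLR feedback form at week 10.
- Partners, control arm: no diary and no form after the start of the study. They have no PLR exposure in the study period, so this matters little.
- Patients who withdraw: no separate step is stated for retrieving the diary. Sample Size anticipates dropout but gives no rate, so the loss cannot be quantified.

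**The case against.** The strongest reply has four parts.

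1. **The contact route is immediate.** A reader who stops at the diary clause might infer that harms are left to the diary alone. The rest of the sentence contradicts that. The route still depends on the participant, so it shortens the delay for those who use it and leaves capture passive.

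2. **Pain is asked about.** A reader might infer that nobody asks about harm at all. The documents do not support this. Deep dyspareunia is scored at each sexual event, pain is recorded site by site at each insert use, and sexual function, distress, anxiety and depression are measured at weeks 4 and 10. An 18-item insert form and a 34-item PLR form are also completed. Their wording is in Multimedia Appendix 1, which is not shown, and they may already ask about problems. This part stands, and it makes the fix conditional. What remains is that the article describes no solicited adverse-event enquiry, and that diary pain scores are also read only at the end.

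3. **Withdrawals are not excluded.** It is tempting to say that the harms of patients who leave are lost. The coordinator follows up with each participant, and the ethics application, cited for further data-management detail, may cover early leavers. Loss is a risk, not a stated consequence. It is also tempting to add that their weeks 1 to 4 pain scores would be lost to the analysis of covariance. A patient who leaves just after week 4 has no weeks 5 to 10 outcome, so her covariate alone would add little, and multiple imputation is planned above 5% missingness.

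4. **An article condenses.** That would answer a complaint about missing detail. Here the article positively describes a passive, end-of-study process, and a better one is available at little cost.

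A reader might also try to size the problem from the upper limit for zero events: 1 − 0.05^(1/20) = 13.9% for 20 PLR users and 1 − 0.05^(1/40) = 7.2% for 40 insert users (one-sided 95%). Those limits come from the pilot's sample size. They would be the same under active enquiry, so they do not measure the effect of passive reporting.

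**Conclusion.** The point holds as a cheap improvement. As described, adverse events reach the team only if the participant writes them in a diary that is read after completion, or makes contact. For a diary-only event, the delay is about 6 to 10 weeks for the insert and at most about 6 weeks for the PLR. Applying 10 weeks to every event would overstate it, because that figure is the outer bound for an event at the very start of the study. Partners have no diary, and recovery of diaries after withdrawal is uncertain.

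The consequence is limited but real: absence of reports could not be taken as absence of harm when deciding on a definitive trial. For the insert, the stated expectation of no adverse events offers no support. Nothing here contradicts another part of the article or changes a stated primary outcome.

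The conclusion rests on three assumptions: diary collection occurs at each participant's completion; no other safety contact is set out in the ethics application; and the feedback forms do not already ask about adverse events. If the second or third fails, the point shrinks accordingly.

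**What to change.** First check the feedback forms in Multimedia Appendix 1 and the ethics application. Unless they already ask:

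- Add one structured adverse-event item, with categories for insert, PLR and other, to the week-4 and week-10 questionnaires that patients in both arms already complete.
- Add the same item to the week-10 PLR form for partners in the PLR arm.
- Review the answers on receipt.
- Collect the weeks 1 to 4 diary pages at week 4, with the questionnaires.
- List adverse events by arm and by device in the results.
- Extend the safety statement in Data Management so that it also addresses the insert.

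The cost is one item on existing forms, one extra return of diary pages, slight added participant burden and a minor ethics amendment. No new contact point is needed.

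The change may reach few participants: 31 couples had been recruited by September 2021 against a target of 40, leaving 40 − 31 = 9 at that date. For those who have already finished, the report should say that adverse-event capture was passive and should not present an absence of reports as evidence of safety.
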